### Interventions

Children are randomised to receive one of the three zinc sulfate regimens (each taken once daily for 14 days): (1) 5 mg; (2) 10 mg or (3) 20 mg. The zinc tablet (all three regimens) ingredients include aerosil, maize starch, ethylvanillin (a vanilla flavour), aspartame, magnesium stearate vegetal and vivapur. The three study tablets have identical appearance, taste and smell. The supplement is a dispersible tablet that dissolves in water or breast milk in about 20 s. The caretakers are instructed to dissolve the tablet in 5–10 mL of water or breast milk immediately before administration. Children receive zinc supplementation for 14 days. The first dose of study drug is given at the health facility in which the child is enrolled.

All three doses of the regimen are packaged identically; 10 tablets in 1 blister, 2 blisters in 1 pack (extra doses are provided for redosing in case of vomiting). Each pack is prelabelled with participant ID. Study regimen is manufactured by Laboratoires Pharmaceutiques Rodael, France and shipped to WHO for randomisation and labelling, before shipment to recruitment sites (as described in ’Randomisation, allocation, concealment and masking' section).

### Adherence assessment

Adherence to the study regimen is optimised by close follow-up: either in person (clinic/home visits) or telephone contact on days 3, 5, 7, 10 and 15. Adherence to the regimen is measured by counting the numbers of unused tablets during each follow-up visit. Study workers/research assistants physically count the tablets during home or clinic visits. We give the mother/caregiver a small booklet to record every successful administration as well as any failed attempts to administer the intervention. Study worker reviews the diary card on each visit and collects filled diary card on day 15 visit.

### Standard of care

All enrolled children receive standard of care for diarrhoea management per WHO/Unicef, Tanzanian and Indian Ministry of Health guidelines. This includes standardised assessment of hydration status, rehydration and maintenance fluids with intravenous or oral rehydration solutions (ORS) as indicated, recommendation for increased fluid intake and continued feeding at home and instructions on when to seek follow-up care. Children with known HIV receive care and treatment appropriate for the child and referral to the care and treatment centre nearest to the child’s home.

### Randomisation, allocation, concealment and masking

Trial arm allocation was performed according to a computer-generated randomisation list (generated off-site by a non-study statistician) of 4500 individuals, stratified by country and child age (>6 to <24 months vs >24 to <60 months). A statistician will hold the randomisation list codes until completion of primary analyses or until requested by the Data and Safety Monitoring Board (DSMB). Within each stratum, subjects are randomly assigned equally in permuted blocks of variable size to receive one of the three doses of zinc. The purpose of the stratification is to have equal distribution of younger and older children among all three treatment groups. An independent pharmacy team prepared the zinc regimen in Geneva by labelling blister packs with participant IDs based on the randomisation list. Labels were printed at WHO, Geneva and enrolled children were assigned sequential serial numbers. These prelabelled regimens were shipped to the sites in Tanzania and India. The packing and physical appearance of the three study regimes are identical. In addition, the three doses of the regimen are similar in taste, appearance and smell. As a result, the research teams, study staff as well as caregivers are fully blinded to treatment arm. Zinc formulations are serially numbered according to the randomisation codes. The code is kept in a password-protected spreadsheet file by WHO personnel and is not available to the investigators until the end of the study. This randomisation list was converted into unique sequential serial numbers for each enrolled child at each site. This code will only be broken if the DSMB requests this information for a participant (should they suspect a relationship of a suspected severe adverse event [SAE] to the study drug) or for a study arm (in their interim analyses).

## Data collection, management and analysis

### Screening and randomisation

Both sites will be recruiting from community clinics. Surveillance systems are set up at clinics to identify all children presenting with diarrhoea. Trained study staff stationed at each health facility are responsible for identification of children who are potentially eligible. The study team is trained in good clinical practice as well as confidentiality and research ethics.

Written informed consent is sought from the caretaker of children meeting the eligibility criteria. A child can only be enrolled once into the study. The informed consent process includes telling the caretaker that they are free to withdraw from the study at any time, and that participation is entirely voluntary.

Following consent, each participant will be assigned a unique subject identification number. A card detailing the subject ID and the health personnel responsible for enrolment will be provided to the caregiver of enrolled children. The patient locator form/subject master log will be the only link between the subject ID and the participant’s name. This information will be stored together with the consent in a locked file cabinet and an online database accessible to only the Project Manager and required study staff for the purpose of patient tracking.

A baseline assessment, including a detailed physical examination (record of vital signs, axillary temperature, respiratory rate, pulse rate, hydration and nutritional status), will be performed by a research physician at the time of screening for enrolment. The child is evaluated for any Integrated Management of Childhood Illness general danger signs (unable/able to drink or breast feed, convulsions, vomiting, unconscious, stiff neck) and evidence of dehydration or pneumonia, as well as information on recent medical history (duration of diarrhoea, bloody stool/dysentery, recent fever). Vital signs (temperature/heart rate/respiratory rate) in dehydrated child are recorded after the child is rehydrated and stabilised and remaining clinical assessment/screening is completed thereafter. Anthropometry measurements will be taken after rehydration and stabilisation as required, before completing the screening for enrolling the participant. Weight will be measured using an electronic scale with a sensitivity of ±10 g by two independent observers: length (for children aged <24 months) or height (for children aged 24 months or older), which will be measured using a length board within 0.1 cm. Mid-upper arm circumference (MUAC) will be measured using non-stretchable tape to the nearest 0.1 cm. All anthropometric measures will be recorded in duplicate (India) and triplicate (Tanzania). Once these measurements and other eligibility criteria are met, the subject will get enrolled.

### Baseline sociodemographic information and vaccination history

Parents of enrolled subjects will be interviewed at study clinic or at home for the baseline sociodemographic characteristics viz. parent’s literacy level and occupation, type of house, possession of assets and possible exposures (recent antibiotic use, travel history, water use and filtration and sanitation), breast feeding and vaccination history and information is recorded in the case record forms.

### Follow-up visits

Scheduled follow-up visits begin from the third day of the enrolment and are generated daily via an automated visit generation module of the data management software. All children enrolled at the study clinic are to be followed up in the clinic or at home by a trained field worker on day 3, 5, 7, 10, 15, 30, 45 and 60 (online supplementary additonal files 1 and 2). In India, study staff will visit the household of enrolled children for all follow-up visitations. If the child is not available at home, a phone call will be made to follow-up the child. In Tanzania, a participant will be followed up at home or clinic on days 3, 7, 15, 30 and 60 and by phone on days 5, 10 and 45. Children still having diarrhoea after day 15 are treated according to standard management guidelines.^8^ At each visitation during active follow-up period, a study worker asks the mother or other caregiver about the following and records the responses in a predesigned form/data entry module:Ongoing symptoms of diarrhoeal illness, including the number and consistency of stools.Vomiting episodes including any episode within 30 min following zinc administration.Adherence with zinc study regimen ascertained via mothers’ recall and/or reported use of zinc tablets by the child in the Diarrhoea Diary Card and cross-checked by determining the number of unused tablets.Any adverse events, including hospital admissions and deaths of study participants.Criteria for returning to clinic (eg, lethargy, poor oral intake, dehydration).Any other intercurrent illness.Reported use of antibiotics and intravenous/other fluids.

At days 30, 45 and 60 postenrolment, the study participants are assessed either at the study clinic, via telephone or with a home visit for presence of any illness, diarrhoea, fever, cough or fast or difficult breathing within last 24 hours and any time in past 2 weeks. On the day 60 study completion clinic visit, in addition to morbidity assessment, anthropometric measurements will be taken for each participant using the same procedure as mentioned in the baseline assessment.

Children not available on the visitation day will be visited the next day; if they are still not available, they are followed-up until found or deemed lost to follow-up. Caregivers are asked to contact the study physicians if they feel that their children are sick between the visits. Children sick on the day of visitation will be referred to the study clinic for a detailed morbidity assessment as well as treatment by the study physician. During each visit, a record of all the medicines and intravenous fluids given, information on number and consistency of stools and data on adherence is recorded in the predesigned forms. Close monitoring will be accomplished through repeated follow-ups during the 14-day regimen period. Every effort will be made to track and successfully follow-up all randomised children.

### Study withdrawal or discontinuation

The participants have the right to withdraw from the study at any time. The subjects will be considered withdrawn from the trial in case of death or lost to follow-up. However, every effort will be made to track and successfully follow-up all enrolled children. The information on withdrawn or discontinued participants will be recorded through a withdrawal slip by field worker and clinic supervisor.

### Blood sampling and laboratory investigations

To allow the measurement of the potential differential impact of the varying zinc doses on plasma zinc levels during the follow-up period, each study participant will provide two blood samples. One-third of the study participants will have blood draws at days 1 and 15, one-third at days 3 and 21 and the remaining one-third on days 7 and 30 postenrolment for assessment of plasma zinc levels.

Blood drawing will follow the protocols of the International Zinc Nutrition Consultative Group (IZINCG). These include use of powder-free gloves, zinc-free syringes and butterfly, needles and trace element-free blood tubes.^14^ Plasma is separated at 15 min after blood collection and aliquots are transferred into trace element-free Eppendorf plastic tubes for temporary storage at −20°C and then shipped to central lab for final storage at −80°C in India. In Tanzania, plasma samples are stored in site refrigerators at 2°C–8°C and then shipped to central laboratory storage at −80°C by the end of the day. Plasma zinc concentrations will be measured by atomic absorption spectroscopy (AAS-400 PerkinElmer, USA).

### Quality assurance

The persons with at least a secondary school degree will be recruited for data collection team. The following quality assurance checks will be done regularly to ensure highest level of data integrity and quality:An extensive 1–3 weeks training session for data collectors to ensure the interdata collector reliability is above 95%.Pilot field data testing is monitored closely by the research scientist(s) responsible for quality assurance.Real-time electronic data capture will ensure data validation such as range, logical checks and data integrity.Interim aggregate data analysis will be carried out periodically for data pattern, heaping, missing values, etc. Based on the feedback, effective measures will be taken to eliminate/minimise the errors.

For overall visit supervision, quality control (QC) supervisors will perform quality checks by visiting at least 10% of the households, re-interviewing 5% respondents and cross-checking these data with concerned field worker. QC supervisors are primarily responsible for overall field-related project activities (data quality and integration at all levels, resolving community issues), and training. Computer randomised list of enrolled children will be used by QC team for random household visits.

The QC team works in close coordination with the investigative team and provides regular feedback on quality issues. Quarterly meetings between QC team and senior investigative team are scheduled to discuss overall quality issues and related corrective measures to be undertaken.

### Data management

Data are collected in real-time using either tablets or laptop computers. Each site uses an in-house designed data management software with user friendly graphical user interface for data collection. Generic case report forms and data dictionary are used to maintain data consistency across sites. In-built range, logical and skipping pattern will ensure data quality and integrity.

The database is password protected with restricted access. Each user is assigned a unique user identifier to access the software and an audit trial is maintained for database operations. The centralised server located at each site synchronises the data on daily basis. Data are shared monthly with WHO data quality monitoring team who is responsible for data quality checks and provide feedback to sites. They generate query forms which are returned to the study sites for verification.

### Data security and storage

A backup of the data is kept in the server at WHO protected by a specific password and accessible to only authorised users. An additional backup of the data is kept in a password-protected external hard drive at a site away from WHO at the recruiting site central offices.

### Record retention and archival

All the study documents including participant’s source data and documents will be archived by the study sites after the completion of the study, till the time WHO informs in writing to the study sites that they no longer need to maintain the study documents.

### Outcome measures

The primary efficacy outcomes are 1) the percentage of enrolled children who have duration of diarrhoea of >5 days, 2) the mean number of loose or watery stools after enrolment and 3) the percentage of children vomiting within 30 min of administration of the zinc tablet.

Secondary outcomes of the trial include: i) proportion of children experiencing SAEs (life-threatening or hospitalisation); ii) proportion with intermediate duration of diarrhoea (diarrhoea continuing beyond 3 days); iii) proportion of guardians with positive attitude towards treatment; iv) treatment adherence; v) mean serum plasma zinc concentration at days 1, 3, 7, 15, 21 and 30; vi) illness symptoms between day 15 and 60 after the treatment 2-week period prevalence and number of days with diarrhoea, fever or respiratory symptoms; vii) 60-day change in height/length, weight, MUAC, height/length-for-age z-score, weight-for-length/height z-score, weight-for-age z-score, MUAC z-score, stunting, wasting, underweight; viii) adherence to regimen; ix) study dropouts; x) maternal report of ease in supplement administration; xi) maternal report of child acceptability; xii) maternal recommendation of use for other children; xiii) maternal report of change in child skin condition, child appetite, activity levels, mood and diarrhoea severity.

### Statistical analysis

All primary analyses of non-inferiority tests will be conducted on the principle of intention-to-treat (ITT). All non-inferiority margins will be defined a priori. We will also conduct sensitivity analyses using a per-protocol (PP) approach.^15^ The analysis population for the ITT approach will include all randomised patients with assessable data, regardless of whether the participant is known to have received a full 14-day dose of zinc or not. The analysis population for the PP approach will include study participants who are documented to have taken zinc supplementation for the first 5 days after randomisation regardless if they vomited the dose. The PP definition was selected due to the primary outcome being diarrhoea duration >5 days. Descriptive statistics will be used to summarise background demographic and baseline clinical characteristics by trial arm.

### Analysis of primary outcomes

#### Primary outcome 1

Number (%) of subjects with diarrhoea episodes >5 days. The last day of diarrhoea will be defined as the day in which there is passage of the last liquid or semi-liquid stool prior to two diarrhoea-free days (days when less than three loose stools/day). The duration of diarrhoea will be defined as the number of days between randomisation (not the reported day of onset of diarrhoea symptoms before randomisation) and the last day with diarrhoea. Children who are lost to follow-up, die or withdraw before 5 days will be excluded from this analysis. For the primary analysis, we have set the threshold for non-inferiority of lower doses of zinc (10 or 5 mg/day) as compared with the standard 20 mg/day at <4% in absolute risk (risk difference) compared with the standard dose in the proportion of subjects with prolonged diarrhoea. The proportions of participants with a prolonged diarrhoea episode (defined as >5 days) will be calculated in all treatment arms, and the risk differences (and their 95% CIs) between the lower doses (5 and 10 mg/day) and the standard dose (20 mg) will be estimated. A Cochran-Mantel-Haenszel approach will be used to take stratifying randomisation factors, for example, country and age groups, into account. If the upper limit of the 95% CI for the risk difference is <4%, we will conclude non-inferiority for one or both lower dose arms. We will also examine the RR of prolonged diarrhoea episodes in both lower dose arms compared with the standard dose arm using RR regression which accounts for factors included in the stratified randomisation. In secondary analyses, Cox proportional hazard models will be used to estimate HRs and their 95% CIs for recovery from diarrhoea in each of the lower dose arms compared with the standard dose arm. The time to recovery is defined as the duration of diarrhoea as noted above.

#### Primary outcome 2

Total number of loose or watery stools after enrolment. An analysis of covariance (ANCOVA) approach will be used to estimate the mean differences and their 95% CI in the total number of loose or watery stools after enrolment for each lower dose arm compared with the standard dose arm, while accounting for the stratified randomisation design. The non-inferiority margin was set at two stools, therefore if the upper limit of the 95% CI is less than two stools, we will reject the null hypothesis that the lower dose zinc is inferior to the standard dose in terms of reducing the total number of loose or watery stools.

#### Primary outcome 3

Vomiting within 30 min after administration of the trial regimen. We hypothesise that the lower dose of zinc will be associated with a reduced risk of vomiting and therefore a superiority test will be used. Vomiting within 30 min of each daily zinc dose is repeatedly measured during the 14-day administration period. Generalised estimating equations (GEE) with the log link, binomial variance and exchangeable correlation matrix will be used to assess the RR of vomiting among the three treatment arms. The exchangeable working covariance matrix and robust estimators of the variances will be used to construct CIs. The robust estimators are consistent estimators of the variances even if the working correlation matrix is misspecified. Stratified randomisation factors will be considered in the model. A secondary analysis concerning severe vomiting (defined as vomiting requiring hospitalisation or vomiting requiring intravenous fluids) will also be performed in similar fashions. We will also examine the proportion of children ever vomiting between the treatment arms and examine whether the RR of vomiting differs by follow-up day.

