### Eligibility

Study participants will be eligible for enrolment in the study if they meet the following inclusion criteria: 1) male and female children between 6 and 59 completed months of age, 2) acute diarrhoea duration of <72 hours at the time of screening (defined as three or more loose or watery stools) or dysentery (defined as visible blood in the stool), 3) likely to stay within the study area for the next 2 months and 4) written informed consent is obtained from caretaker.

Children will be excluded if they: (1) have severe acute malnutrition (weight for length/height z-score of <−3 or oedema), (2) have severe dehydration that cannot be corrected within 4–6 hours, (3) have signs of severe pneumonia (characterised by presence of either chest in-drawing and either of the following: convulsions or unconscious or vomiting everything,^13^ sepsis, rapid diagnostic test (RDT)-confirmed malaria or other severe illness, (4) have previously or currently been enrolled in the study, (5) are currently enrolled in another trial, (6) are not intending to remain in study area for the duration of the study, (7) have a caregiver who declines participation in the study, (8) have other child currently enrolled in the study in the same household and (9) have used zinc supplements during the 3 days preceding study enrolment.

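### A child can enter on visible blood alone, but the end of the episode is judged on loose stools only; such children, of unknown number, dilute outcome 1 towards non-inferiority

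*Protocol article*

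**What the plan says.** All references are to the Protocol article.

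- **Eligibility** gives two alternative entry routes: acute diarrhoea, "defined as three or more loose or watery stools) or dysentery (defined as visible blood in the stool". The second route carries no stool count.
- **Analysis of primary outcomes, Primary outcome 1** places the last day of diarrhoea at the last liquid or semi-liquid stool "prior to two diarrhoea-free days (days when less than three loose stools/day". Visible blood is not mentioned. Duration is "the number of days between randomisation (not the reported day of onset of diarrhoea symptoms before randomisation) and the last day with diarrhoea". The Cox analysis uses the same rule: "The time to recovery is defined as the duration of diarrhoea as noted above".
- **Follow-up visits** lists what is asked at each contact, including "Ongoing symptoms of diarrhoeal illness, including the number and consistency of stools". Blood is not named, although the list is not worded as exhaustive.
- **Screening and randomisation** records bloody stool or dysentery in the baseline history. **Sensitivity analyses and modification of treatment effect** uses dysentery at enrolment as one of many exploratory effect modifiers.
- No section gives a separate recovery rule for children who enter on dysentery.

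**The concern.** Blood is enough to start an episode but is ignored in ending it. A child who qualifies on blood while passing nought, one or two loose stools a day already meets the rule for a diarrhoea-free day at randomisation. The outcome is then settled by how the child entered, not by the dose received.

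Such children add to the denominator of every arm and add no events, so they shrink the risk difference between a lower dose and 20 mg. In a superiority test that would be conservative. In a non-inferiority test against a fixed 4-point margin it makes the favourable conclusion easier to reach. The planned per-protocol analysis offers no protection, because it selects on doses taken in the first 5 days and keeps these children.

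Both definitions are written out in the article, so this is a mismatch between stated rules and not a detail left to the analysis plan.

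**Working it through.** **1. Apply the rule to the child in question.** Take a child entered on blood, with fewer than three loose stools on each of the first two days after randomisation. Both days are diarrhoea-free as defined. The last liquid or semi-liquid stool before them, if there was one, fell at or before randomisation. Duration from randomisation is therefore zero, or has no defined end day. Either way the enrolled episode is not scored as over 5 days, however long blood persists. A child with blood and three or more loose stools a day is timed like any other.

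**2. Reproduce the plan's figure.** Table 1 gives 1500 per arm for 16% v 16%, margin 4 points, 90% power, 5% significance and about 5% attrition.

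n = (z₁₋α + z₀.₉₀)² × 2 × 0.16 × 0.84 / 0.04²

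- One-sided α = 0.05: 1439, or 1439/0.95 = 1515 with attrition, within about 1% of 1500.
- One-sided α = 0.025: 1766, or 1859 with attrition, which does not match.

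The definition mismatch does not depend on this figure. The decision rule is an upper 95% limit below 4 points, read here as two-sided, so one-sided 2.5% is used below.

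**3. Size of the dilution.** Inputs:

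- Control risk 16% and margin 4 points (Table 1).
- Evaluable children per arm: 1500 × 0.95 = 1425.
- Share s of affected children: **assumed**, since the document gives none; the range is 2% to 10%, the same in each arm.
- True difference among the other children: set at the margin, 16% v 20%.
- Affected children: no events in any arm.

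Observed risks are 0.16(1−s) and 0.20(1−s), so the observed difference is 0.04(1−s).

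SE = √{[p₁(1−p₁) + p₂(1−p₂)]/1425}

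P(declare non-inferiority) = Φ{[0.04 − 0.04(1−s)]/SE − 1.96}

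| s | Risks | Difference (points) | SE | Φ argument | P |
|---|---|---|---|---|---|
| 0 | 16.00% v 20.00% | 4.00 | 0.01437 | −1.960 | 2.5% |
| 2% | 15.68% v 19.60% | 3.92 | 0.01426 | −1.904 | 2.8% |
| 5% | 15.20% v 19.00% | 3.80 | 0.01409 | −1.818 | 3.5% |
| 10% | 14.40% v 18.00% | 3.60 | 0.01379 | −1.670 | 4.7% |

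This is a normal approximation without stratification. At one-sided 5%, the level that reproduces Table 1, the same calculation gives 5.0%, 5.6%, 6.6% and 8.8%.

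**4. Precision lost by leaving these children out.** With 16% in both arms and 1425(1−s) children per arm, the 95% half-width is 1.96 × √{2 × 0.16 × 0.84/[1425(1−s)]}. It goes from 2.69 points with none removed to 2.72, 2.76 and 2.84 points at s = 2%, 5% and 10%.

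**The case against.** **The affected group may be tiny.** The article describes its population as children with acute diarrhoea, and nothing shows that any child entered on blood with fewer than three loose stools a day. This stands: the size is unknown. A reader might infer that every child with dysentery is counted as recovered from the start. The documents do not support that, because those with frequent loose stools are timed normally.

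**The probabilities in the table are not type I error.** If the other children differ by 4 points and the affected children have no events, the difference across all enrolled children on the stated outcome is below 4 points. Declaring non-inferiority for that population is then correct. This also stands. A reader might take 4.7% against 2.5% as an inflated error rate for the trial's test; it is an error only with respect to children who can have the event. What remains is that children whose outcome is fixed at entry carry no information on dose.

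**Adding blood to the endpoint would change it.** The 16% rate and the 4-point margin were set for diarrhoea duration. Persistence of blood would make a composite with no documented event rate. Enrolment began in January 2017 and only 742 children were still contributing data on 1 February 2019, so a new follow-up item would come too late for most. This stands, and it is why the primary definition should not be changed.

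**The dysentery subgroup analysis already covers it.** Only in part. It is exploratory, by the article's own account probably underpowered, tied to no non-inferiority decision, and it does not separate blood alone from blood with frequent loose stools.

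**Outcome 2** might seem to share the fault. It does not: "Total number of loose or watery stools after enrolment" is by name a count of loose or watery stools, and leaving out other stools is its definition.

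**Conclusion.** The entry and end-of-episode definitions do not match. For children who enter on blood with fewer than three loose stools a day, the enrolled episode cannot be scored as over 5 days in any arm. The effect on outcome 1 is dilution towards non-inferiority, and the Cox analysis inherits the same rule.

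The size rests on an assumed share. At 2% to 10%, a true 4-point difference in the other children appears as 3.92 to 3.60 points, and the chance of declaring non-inferiority rises from 2.5% to between 2.8% and 4.7%. This assumes equal shares across arms, no events in the affected children and 1425 evaluable per arm. If the children are few, the effect is negligible. The point justifies a prespecified sensitivity analysis, not a new primary endpoint.

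**What to change.** 1. Keep the stool-frequency definition for the primary analysis of outcome 1.
2. Report, by arm, the number of children who entered on blood without three or more loose stools.
3. Before unblinding, prespecify a repeat of the outcome 1 non-inferiority test and the Cox analysis without these children, and require the non-inferiority conclusion to hold in both sets. Exclusion rests on a criterion assessed at screening, before randomisation, so the randomised comparison is preserved.
4. If visible blood was recorded at follow-up, add a sensitivity definition in which a diarrhoea-free day also requires no visible blood.

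The cost is a short addition to the analysis plan and a slight loss of precision (half-width up by 0.03 to 0.15 points at shares of 2% to 10%). Step 3 needs the entry route or screening stool count to be retrievable. The article lists bloody stool in the baseline history but not the count, although the entry criterion requires it to be assessed; this should be checked in the case report forms.

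### The primary non-inferiority analysis of diarrhoea >5 days excludes every child who dies, withdraws or is lost before day 5, including children with a known outcome, which conflicts with the protocol's own intention-to-treat set

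*Protocol article*

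**What the plan says.** All places are in the protocol article.

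- **Analysis of primary outcomes, Primary outcome 1:** "Children who are lost to follow-up, die or withdraw before 5 days will be excluded from this analysis". No exception is given.
- **Same section, end of episode:** the last day of diarrhoea is fixed by "passage of the last liquid or semi-liquid stool prior to two diarrhoea-free days", and duration is counted from randomisation.
- **Statistical analysis:** the primary non-inferiority tests are to follow intention-to-treat, and "The analysis population for the ITT approach will include all randomised patients with assessable data". A per-protocol analysis is the stated sensitivity analysis. It is limited to children with documented zinc intake over the first 5 days.
- **Outcome measures:** the endpoint is "the percentage of enrolled children who have duration of diarrhoea of >5 days".
- **Study withdrawal or discontinuation:** "The subjects will be considered withdrawn from the trial in case of death or lost to follow-up".
- **Decision rule (Primary outcome 1):** non-inferiority is concluded if the upper 95% limit of the risk difference is below 4 points.

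**The concern.** The exclusion depends on when a child leaves, not on whether the outcome is known. That creates two conflicts.

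1. **Known recoveries are discarded.** The end-of-episode definition lets recovery be established before day 5. Such a child has assessable data and belongs in the intention-to-treat set, yet the exclusion sentence removes the child if lost on day 4.
2. **Deaths are deleted.** A child who dies in the first 5 days without having recovered is an enrolled child for whom treatment did not succeed. The rule takes that child out of both numerator and denominator.

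At stake is the non-inferiority decision on a primary outcome. Exclusions made after randomisation can differ between arms, and a difference of a point or two matters when the margin is 4 points and the confidence interval uses up most of it. No other described analysis is stated to bring these children back: the per-protocol set is smaller, and the covariate-adjusted, relative-risk and Cox analyses are not said to use a wider set.

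**Working it through.** **Inputs.** From the sample size section and Table 1: 16% events in each arm, margin 4 points, 90% power, 1500 per arm, 5% loss to follow-up. From Primary outcome 1: the 95% CI rule. From Follow-up visits: the contacts in the first 5 days are on days 3 and 5. The number excluded before day 5 is not given, so every exclusion rate below is an assumption.

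**The plan's own figure.** Evaluable n per arm = 2 × 0.16 × 0.84 × (z_α + z_β)² / 0.04².
- One-sided 5%: 0.2688 × (1.645 + 1.282)² / 0.0016 = 1439. Divided by 0.95 this is 1515, which agrees with the stated 1500.
- One-sided 2.5%, which matches a 95% CI rule: 1766 evaluable and 1859 after inflation, which does not reproduce 1500. That mismatch is a separate matter. Here it means only that the confidence interval is wide relative to the margin.

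**A known outcome that is dropped.** Suppose a child's last loose stool is on day 1 and days 2 and 3 are diarrhoea-free. At the day 3 contact the episode has ended and the outcome is known: not >5 days. If the child is lost on day 4, the assessable-data definition keeps the child and the exclusion sentence removes the child.

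**Room left before the margin.** With 1425 analysed per arm (1500 × 0.95):
- SE = √(2 × 0.16 × 0.84 / 1425) = 1.373 points.
- Half-width = 1.96 × 1.373 = 2.69 points.
- Largest observed difference that still passes = 4 − 2.69 = 1.31 points.

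**Scenarios.** Take 16% failures among analysed children in both arms, restore all 1500 per arm, and count every excluded child as a failure. With exclusion fractions d_L (low dose) and d_S (standard), each arm's rate is (1 − d) × 0.16 + d, so the difference is 0.84 × (d_L − d_S). The limits are unstratified.

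| Excluded, low dose | Excluded, standard | Difference (points) | Upper 95% limit (points) |
|---|---|---|---|
| 5% | 5% | 0 | 2.87 |
| 6% | 4% | 1.68 | 4.55 |
| 7% | 3% | 3.36 | 6.23 |
| 2% | 1% | 0.84 | 3.54 |
| 0.5% | 0.1% | 0.34 | 2.98 |

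For the 6% versus 4% row the rates are 0.94 × 0.16 + 0.06 = 21.04% and 0.96 × 0.16 + 0.04 = 19.36%. The SE is √((0.2104 × 0.7896 + 0.1936 × 0.8064) / 1500) = 1.466 points, and 1.68 + 1.96 × 1.466 = 4.55.

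**The other direction.** With the same fractions swapped (4% low dose, 6% standard), the difference is −1.68 and the upper limit is −1.68 + 2.87 = 1.19. If the excluded children had instead all recovered, dropping 5% of an arm as non-events raises its observed rate from 16.0% to 0.16 / 0.95 = 16.8%.

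**The case against.** Several objections have force.

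- **The analysis set is defined openly.** The article limits intention-to-treat to children with assessable data, so leaving out a child whose outcome is truly unknown is consistent with its own definition. This stands. The conflict is confined to known recoveries and deaths.
- **The direction of bias is not established.** A reader might infer that failures leave the low-dose arms and that the rule therefore favours non-inferiority. The article does not support this. Loss can follow recovery as well as failure. Only for deaths is the direction certain: each deletion lowers the failure rate in that child's arm, and the effect on the difference still depends on how deaths split between arms.
- **The 5% is the wrong quantity for early loss.** It is planned attrition in a trial with 60 days of follow-up, and contacts on days 3 and 5 should keep early loss well below it. This stands, so the scenarios near 5% are an upper range. Larger biases, up to the whole margin, can be obtained only by assuming very different failure rates among excluded children by arm, for which the article gives no basis.
- **Deaths are not invisible.** The SAE outcome names "proportion of children experiencing SAEs (life-threatening or hospitalisation") and not death. A reader might infer that an early death appears in no outcome. But deaths are recorded at follow-up visits and classed as withdrawals, and study dropouts are a listed secondary outcome.
- **Other inferences go too far.** No text removes hospitalised children. Nothing says that truncated stool counts enter outcome 2 as totals, or that a child lost on days 5 to 7 with unknown status is kept. The unseen SAP may cover these.

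The SAP may also hold missing-data analyses, and their absence from the article is not the point. The point is the exclusion rule that the article states.

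**Conclusion.** The concern holds in a limited form. As written, the exclusion sentence contradicts the assessable-data definition for children already known to have recovered, and it removes early deaths from an endpoint defined on enrolled children. The planned per-protocol analysis does not repair either.

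The size of the effect cannot be computed from the article. The scenarios rest on assumed exclusion rates, on 16% failures among analysed children in both arms, and on every excluded child being a failure. Under them, a 2-point imbalance (6% versus 4%) is enough to reverse a non-inferiority conclusion, because only about 1.3 points of room exist. Exclusions on the scale of deaths alone (0.1 to 0.5%, assumed) shift the difference by about 0.3 points and would not reverse it. The case for changing the rule is that it discards known information and leaves the primary conclusion open to an imbalance that cannot be foreseen. It is not that a bias towards non-inferiority has been shown.

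**What to change.** Replace the exclusion sentence under Primary outcome 1 with three rules:

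1. A child whose two diarrhoea-free days were observed before leaving keeps that outcome, whenever the child left.
2. Death before recovery counts as not recovered, that is, as diarrhoea >5 days.
3. Children whose outcome is truly unknown are multiply imputed using arm, randomisation strata and stools up to the time of loss. A tipping-point analysis then shows how unfavourable the imputed low-dose outcomes must be before the upper limit reaches 4 points.

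Counting death as a failure is one defensible convention. It should be fixed in advance. If the SAP already contains such rules, the article's sentence should be brought into line with it. The change should be made while the analysts are blind; the article keeps the codes closed until the primary analyses are complete unless the DSMB asks for them.

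Cost: revised wording, a little more analysis and slightly wider intervals. No new data are needed.
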